### Secondary outcome measures

Corneal thickness (CT), anterior chamber depth (ACD), and lens thickness (LT) were measuredwith a Lenstar LS900 (Haag-Streit, Koeniz, Switzerland) together with AL. Five measurements were taken, and the average value per eye was used for further data analysis. Distance-corrected visual acuity (DCVA) is evaluated using a standard 100% contrast English Early Treatment Diabetic Retinopathy Study (ETDRS) logMAR chart at 4 m with usual correction or new distance prescription. DCVA is scored using the standard technique of subtracting 0.02 logMAR units for each correctly identified optotype.

### Study equipment questionnaire

The questionnaire contains six questions. The first four questions evaluate adaptation and subjectively evaluate various aspects of vision with the study equipment on a scale of 1 to 10. Question 1 quantifies the clarity of vision (1 = blurred, 10 = clear); question 2 evaluates the perception of ghost images (1 = none, 10 = severe); question 3 evaluates satisfaction with the study equipment (1 = not satisfied, 10 = satisfied), and question 4 evaluates the comfort of the study equipment (1 = uncomfortable, 10 = comfortable). The remaining questions assess compliance in terms of how long the study equipment is worn (question 5: hours per day, and question 6: days per week).

### Study visits and procedures

The procedures performed at each visit are summarized in Table 1.

**Table 1 Tab1:** Visit schedule for the study. V1 to V7 represent visits 1 through 7. AL Axial length, *CT* Corneal thickness, *ACD* Anterior chamber depth, *LT* Lens thickness, *DCVA* Distance-corrected visual acuity

Visit schedule	V1	V2	V3	V4	V5	V6	V7
Informed consent	X						
Eye examination	X						
Inclusion and exclusion criteria	X						
Study frame choice	X						
Monocular pupillary distance and fitting measurements	X			X			
Washout spectacles delivery	X						
Study spectacles delivery		X			X		
AL, CT, ACD and LT measurements	X	X	X	X	X	X	X
Cycloplegic autorefraction	X				X		X
Non-cycloplegic subjective refraction	X			X			
DCVA	X	X	X	X	X	X	X

During the recruitment and baseline visit (V1), we first performed a full ocular examination, including presenting visual acuity, objective and subjective refraction, anterior segment and fundus inspection, and binocular vision status (near and far phoria, near point of convergence (NPC), Worth 4-dot test), followed by acquisition of the primary outcome measures (cycloplegic SER and AL) and all secondary outcome measures (DCVA, AL, CT, ACD, and LT). The subjects chose their frame, and the same frame was used for SAL and control single vision lenses, i.e., before and aftercrossover. At the end of the baseline visit, the subjects are dispensed with washout single vision lenses corresponding to the prescription for their first study equipment.

The main follow-up visits included the 6-month crossovervisit (V5) and the final 12-month visit (V7) with all primary outcome measures, including the questionnaires.

The additional study visits comprise the dispensing visit (approximately one month after the baseline, V2), 3-month (V3), 5-month (V4), and 9-month visits (V6) with only noncycloplegicAL and secondary outcome measures. In addition, at the 5-month visit, we acquired noncycloplegicsubjective refraction as a basis for the prescription for the study equipment worn during the second phase of the study (i.e., aftercrossover). Before ordering a new prescription, trial frame was used to confirm comfort of each participant.

Between one and three days after the dispensing visit and 6-month visit, we administered the compliance and adaptation questionnaire over the phone.

During all study visits, the study equipment was adjusted, and subjects were instructed to wear it at least 7 h per day.

Cycloplegia is always induced by 1% cyclopentolate hydrochloride (Alcon Laboratories) eyedrops delivered three times, five minutes apart after induction of corneal anaesthesia with proparacaine (0.5% Alcaine, Alcon Laboratories).

### Data analyses

#### Baseline data analyses

Paired-sample t testwere used for within-subject interocular comparisons and independent-sample t test- were used for between-group comparisons. Bivariate correlations were used to evaluate the relationships between outcome measures. Sincethe -intereye correlation for ocular parameters was high, only the right eye data wereanalysed. Statistical analyses were performed using SPSS 16.0 (SPSS Inc., Chicago, IL, USA).

#### Prospective data analyses

The changes in spherical equivalent cycloplegic autorefractiveerror and AL between the follow-up and baseline data will be used to evaluate myopia progression. Myopia progression and axial elongation will be compared between the SAL lenses and the single vision lenses using independent-samplet test. A multivariate regression model will be used to evaluate the relationships between variables such as age, gender, baseline myopia, parental myopia, NPC and phoria level, and myopia progression.

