## Methods

### Study design

This is a prospective, double-masked, crossover, and randomized clinical trial. The duration of the study is 13 months (see Fig. 1 for more details about the timeline of this study), and it consists of 7 visits.

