**Fig. 1 Fig1:**
[figure not shown]
Flow chart of the study; M – month(s), W – week(s)

Eligible subjects were randomized into two groups. Group 1 will wear SAL lenses for 6 months, followed by 6 months of wearing single vision lenses. In Group 2, the order in which the lenses are worn is reversed. In this paper, we refer to the spectacles worn during the first 6 months (regardless of lens type) as study equipment 1 and the spectacles worn during the second 6 months (regardless of lens type) as study equipment 2 (Fig. 1). At each visit, all subjects were instructed to wear the study equipment for more than seven hours every day.

The study is being conducted at the Hangzhou Branch of Zhejiang Eye Hospital Affiliated to Wenzhou Medical University. The study and its protocol followed the tenets of the Declaration of Helsinki and were approved by the institutional review board of the Eye Hospital of Wenzhou Medical University. Written informed consent was obtained from participants and their guardians after a detailed explanation of this study and the possible risks and benefits at the first visit. The study is registered at the Chinese Clinical Trial Registry (ChiCTR1900021002, 24/01/2019).

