### Study participants

A total of 100 children were recruited from the hospital into this study between January and March 2019. The inclusion criteria were best-corrected visual acuity equal to or better than 1.0, age between 8 and 13 years inclusive, spherical equivalent of cycloplegic autorefraction between -0.75 D to -4.75 D in each eye, astigmatism no more than 1.50 D, anisometropia no more than 1.00 D, and absence of strabismus. Subjects with a history of ocular or systemic disease, history of wearing PALs, or prior myopia control treatment were excluded from participation in the study.

The study was designed to achieve 80% power to detect a minimum difference of 0.27 D with an SD of 0.37 D at 6 months at a 5% level of significance. Using an online sample size calculator by the Clinical & Translational Science Institute33, the theoretical sample size was 42 with a 1:1 sample ratio in each group. Allowing a maximum drop-out rate of 15%, the number to be recruited for each group was estimated to be 50.

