## Discussion

Although numerous interventions are currently available to slow myopia progression, it still be beneficialfor young children to develop effective and safe strategies for myopic retardation. Spectacle lenses with contiguous aspherical lenslets may be an interesting option. At present, there are few reports on the myopia control effect of these lenses. From this perspective, we conducted a double-masked, crossover, randomized clinical trial to assess the efficacy of spectacle lenses with rings of contiguous slightly aspherical lenslets.

We followed 100 children randomized into two groups of 50. The two groups were well matched for the main covariate parameters, such as age, spherical equivalent refractive error, and AL (0.49 < p < 0.94), minimizing their effects on the results of the study.

In this study, we adopted a one-year crossoverdesign that is not very common in myopia research. We believe that this approach has merit, particularly for completely novel interventions whose myopia control effect is difficult to infer from previous studies. Unlike regular clinical trial design, this crossoverdesign may provide a within-subject treatment comparison with little to no influence of genetics and other subject-specific factors. However, it must be noted that these analyses should be interpreted with caution because they may be biased by possible carry-over effects or difficulty with subject masking.

We also opted to have a shorter interval (maximum of 3 months) between the study visits; that is, a maximum of 3 months versus the more standard 6 months. This decision was motivated by the interest in evaluating the myopia control effect of SAL lenses at finer temporal resolution. Although cycloplegic SER and AL are only taken at baseline, and at the 6- and 12-month visits to minimize cycloplegia, we believe that these data will provide valid evidence for the effect of myopia control.Moreover, AL without cycloplegia will be taken at the 3-, 5-, and 9-month visits, and these data will be informative. First, the AL is considered animportant index to evaluate myopic progression [34, 35]. Second, previous research has indicated that (lack of) cycloplegia has no significant effect on AL [36]. In addition, 3-month visits may allow better compliance through parent and child engagement and, more often, equipment checks.

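### The independent-sample t test named for both main outcomes does not deliver the within-child comparison that justifies the crossover, and its standard error is wrong if the two periods are pooled by lens

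*Protocol article*

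**What the plan says.** All references are to the protocol article; no separate analysis plan is at hand.

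- **Design** (Study design): "This is a prospective, double-masked, crossover, and randomized clinical trial". "Group 1 will wear SAL lenses for 6 months, followed by 6 months of wearing single vision lenses"; Group 2 has the reverse order. Each child therefore contributes a 6-month period on each lens.
- **Test** (Prospective data analyses): "Myopia progression and axial elongation will be compared between the SAL lenses and the single vision lenses using independent-samplet test". No pairing, period or sequence term is named, nor the period or periods used.
- **Response** (same section): "The changes in spherical equivalent cycloplegic autorefractiveerror and AL between the follow-up and baseline data will be used to evaluate myopia progression". Which visit serves as baseline for the second period is not stated.
- **Rationale** (Discussion): "this crossoverdesign may provide a within-subject treatment comparison with little to no influence of genetics and other subject-specific factors". Carry-over is named there as a caution.
- **Sample size** (Study participants): "80% power to detect a minimum difference of 0.27 D with an SD of 0.37 D at 6 months at a 5% level of significance", and "the theoretical sample size was 42 with a 1:1 sample ratio in each group".
- **Baseline data analyses** assigns paired t tests to within-subject (interocular) comparisons and independent-sample t tests to between-group comparisons.

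**The concern.** The contrast is worded as one between lenses, in a trial where both lenses are worn by the same children. Read that way, 100 changes on SAL are set against 100 changes on single vision lenses as though they came from 200 children. The standard error then ignores the within-child correlation, and the p values for both main outcomes inherit the error.

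Read the other way, as Group 1 against Group 2 within a period, the arithmetic is sound, but the within-child contrast offered as the merit of the design is never estimated.

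The period also deserves a place in the model. Enrolment was short ("A total of 100 children were recruited from the hospital into this study between January and March 2019"), so the two periods fall in different seasons for nearly everyone, and all children are six months older in the second.

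The change score adds to the ambiguity. Study visits and procedures calls V1 the baseline visit. If V1 is the reference throughout, the change to V7 spans both lenses in both groups and does not isolate a lens effect.

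**Working it through.** **Inputs.** SD 0.37 D, difference 0.27 D, 42 per group before and 50 after a 15% dropout allowance (Study participants). I take 0.37 D as the SD of a 6-month change and tests as two-sided at 5%. The documents do not give rho, the size of a period effect, or the measurement error of SER; ranges below are assumptions.

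**1. The plan's own figure.** n per group = 2 × (1.96 + 0.84)² × (0.37/0.27)² = 29.5, so 30 (31 with the t distribution), not 42. With 42 per group, power for 0.27 D is about 92%. The dropout step does reproduce: 42/0.85 = 49.4, so 50. The 42 is a separate matter. What counts here is that the formula is a parallel two-group one and supplies the SD.

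**2. Both periods pooled by lens, N = 100 children, no period effect.**
- SE used by the independent test = 0.37 × √(2/100) = 0.0523 D.
- True SE = 0.37 × √(2(1 − rho)/100).
- Actual type I error = 2 × [1 − Φ(1.96 × SE used / true SE)].

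| rho | SE used (D) | True SE (D) | Used/true | Type I error |
|---|---|---|---|---|
| -0.3 | 0.0523 | 0.0597 | 0.88 | 8.6% |
| -0.2 | 0.0523 | 0.0573 | 0.91 | 7.4% |
| 0 | 0.0523 | 0.0523 | 1.00 | 5.0% |
| 0.3 | 0.0523 | 0.0438 | 1.20 | 1.9% |
| 0.5 | 0.0523 | 0.0370 | 1.41 | 0.6% |
| 0.7 | 0.0523 | 0.0287 | 1.83 | 0.03% |

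The ratio does not depend on N. With 84 completers the SE used is 0.0571 D and the type I errors are the same.

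**3. Sign of rho.** A stable tendency of a child to progress fast or slowly makes rho positive. The V5 measurement ends the first change and starts the second, so its error enters with opposite signs and contributes −(error SD)²/0.37² to rho: −0.16 for an assumed error SD of 0.15 D, −0.29 for 0.20 D. The net sign cannot be settled from the documents.

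**4. Period effect in the pooled test.** With equal sequences, each lens mean holds half its observations from each period, so a period effect cancels from the mean difference. It only widens the SE used: for 0.2 D, √(0.37² + 0.2²/4) × √(2/100) = 0.0542 D. With unequal sequences n1 and n2 the bias is the period effect × (n2 − n1)/(n1 + n2). With 50 and 42 completers and 0.2 D, its size is 0.2 × 8/92 = 0.017 D.

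**5. Groups compared within the first period, 42 per group.** SE = 0.37 × √(2/42) = 0.0807 D. The test is valid (simulated type I error 4.7% to 5.2%) and both groups share the period. The crossover analysis on the same 84 children has SE 0.37 × √(2(1 − rho)/84): 0.0651 D at rho -0.3, 0.0571 D at 0, 0.0478 D at 0.3 and 0.0404 D at 0.5.

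**6. Simulation** (20,000 trials, 42 per sequence). Comparing within-child period differences between sequences held 4.9% to 5.3% type I error for rho from -0.3 to 0.5, with and without a 0.2 D period effect. For an assumed lens effect of 0.12 D, period effect 0.2 D and rho 0.5, power was 53% pooled, 84% for the crossover analysis and 32% for the first period alone.

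**The case against.** The strongest reply is that the test was never meant for pooled data. The sample size is a parallel calculation at 6 months; the Fig. 2 caption and Table 4 use SAL and SVL as labels for Group 1 and Group 2 in the first phase; and the baseline section reserves independent-sample tests for between-group comparisons. On that reading the standard error and p value are correct, season and age are common to both groups, and 42 per group gives ample power for 0.27 D. This stands. A reader might infer from the wording of the test that the standard error and p value are simply wrong; the documents do not support that without the pooling, which they permit but do not state.

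Two further temptations fail. One is that ignoring the period biases the lens effect: with balanced sequences it does not. The other is that the pooled test produces false positives: that needs negative rho, whereas the Discussion's appeal to subject-specific factors points towards positive rho and a conservative test. The argument from V5 error was quantified for SER only; AL is an average of five readings.

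It may also be said that a t test on period differences between sequences is itself an independent-sample test, and that an article leaves such detail to the full plan. The first is true, but the article describes a test on progression by lens, not on period differences. The second does not dispose of the point, because a test is stated and, as stated, does not match the rationale given for the design.

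**Conclusion.** The point holds in conditional form. Under neither of the two readings set out here does the named test give the within-child comparison claimed for the crossover.

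- **Pooled by lens:** the standard error is wrong unless rho is 0. At SD 0.37 D and no period effect it is 41% too large at rho 0.5 and about 9% too small at rho -0.2. The direction depends on a correlation the documents do not give. A period effect adds some width, and adds bias only if dropout unbalances the sequences.
- **Between groups within one period:** the inference is valid, but in the first period the standard error is twice that of the crossover analysis at rho 0.5 (0.0807 against 0.0404 D) and 1.41 times at rho 0 (0.0807 against 0.0571 D), with 42 per group.

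Confidence is high that test and rationale do not match. Which reading was intended, and hence whether any p value would be wrong, cannot be determined from the article. No size is given for AL because the article gives no SD for its change.

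**What to change.** State the following before analysis:

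1. **Change scores.** Period 1 is V5 minus the pre-treatment baseline; period 2 is V7 minus V5. For SER the pre-treatment value can only be V1, since Table 1 has no cycloplegic refraction at V2. That change therefore also covers the washout month, a further reason for a period term. For AL, say whether V1 or V2 is used.
2. **Comparison using both periods.** For each child take the period 1 change minus the period 2 change, compare this between the two sequence groups, and halve the difference in means. Alternatively, fit a mixed model with lens, period and sequence as fixed effects and child as random effect. A random intercept cannot represent a negative within-child correlation, so an unstructured covariance for the two periods is safer for SER.
3. **First period alone.** Keep the independent-sample t test for Group 1 against Group 2, which is free of carry-over between the study lenses.
4. **Priority.** Say which of items 2 and 3 is primary.

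The cost is a paragraph of analysis wording, with no new data or visits.

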## Results

### Overall baseline data

We recruited 102 children from the Hangzhou Branch of Zhejiang Eye Hospital. One child dropped out just after the randomization period for personal reasons. One child was excluded from the study because of his or herlarge magnitude of phoria that manifested before the dispensing visit. Thus, the data from 100 children (54 males and 46 females) aged 8 to 12 years old (mean age, 9.49 ± 1.42 years) were analysed and are reported in this paper. We found no significant difference in the SER or AL between the eyes (t = 1.11, *p* = 0.27, 95% CI: -0.03659, 0.12879 and t = -1.04, *p* = 0.30, 95% CI: -0.05951, 0.01867 respectively).

The mean AL was 24.84 ± 0.76 mm (range: 23.13 to 26.86 mm), and the mean SER was -2.69 ± 0.86 D (range: -1.00 to -4.50 D). These two measures were significantly correlated (r = -0.432, *p* < 0.001).

More details on the baseline values, including the secondary outcome measures, can be found in Table 2.

**Table 2 Tab2:** Baseline characteristics of the subjects and interocular comparison. Data are expressed as the mean ± *SD*. *SER*, Spherical equivalent refractive error, *AL* Axial length, *CCT* Central corneal thickness, *ACD* Anterior chamber depth, *LT* Lens thickness, t/p, paired-sample t-tests were used to compare the values between the two eyes

	Age (years)	SER (D)		AL (mm)		CCT (µm)		ACD (mm)		LT (mm)	
		OD	OS	OD	OS	OD	OS	OD	OS	OD	OS
Minimum value	8	-4.50	-4.75	23.13	22.84	473.40	480.00	2.76	2.73	2.97	3.00
Maximum value	12	-1.00	-1.13	26.86	27.05	603.60	614.80	3.80	3.77	3.61	3.65
Mean value	9.49 ± 1.42	-2.69 ± 0.86	-2.74 ± 0.94	24.84 ± 0.76	24.86 ± 0.76	545.20 ± 26.78	546.02 ± 27.61	3.25 ± 0.20	3.25 ± 0.20	3.32 ± 0.15	3.32 ± 0.15
Differences between two eyes	-	0.33 ± 0.26		0.16 ± 0.12		3.80 ± 4.57		0.03 ± 0.03		0.02 ± 0.03	
t value	-	1.11		-1.04		-1.39		0.46		-1.23	
*p* value	-	0.27		0.30		0.17		0.65		0.22	

### Between-group comparison of baseline data

Eligible subjects were randomized to two groups of 50 subjects. The mean age was 9.48 ± 1.36 years (range: 8 to 12) in Group 1 and 9.50 ± 1.50 years (range: 8 to 12) in Group 2. There was no significant difference between the groups (t = -0.07, *p* = 0.94).

The two groups were matched for SER and AL. The mean AL was 24.79 ± 0.67 mm (range: 23.35 to 26.59 mm) in Group 1 and 24.89 ± 0.84 mm (range: 23.13 to 26.86 mm) in Group 2. The mean SER was -2.68 ± 0.83 D (range: -1.25 to -4.50 D) in Group 1 and -2.72 ± 0.90 D (range: -1.00 to -4.50 D) in Group 2. There was no significant difference between the groups for AL or SER (t = -0.69, *p* = 0.49 and t = 0.22, *p* = 0.83, respectively). SER and AL were negatively correlated in both groups (Group 1:r = -0.309, p = 0.029; Group 2:r = -0.506, *p* < 0.001; Fig. 2).

**Fig. 2 Fig2:**
[figure not shown]
Distributions and relationships between the primary outcome measures at baseline. Left panel – axial length (AL), middle panel – cycloplegic spherical equivalent (SER), right panel – correlations between AL and SER. Lighter shade shows Group 1 (SAL); darker shade Group 2 (single vision lens; SVL). Triangles filled with the corresponding shade indicate the groups’ means

There were no significant differences between the groups for any of the secondary outcome measures (-0.88 < t < 1.06, 0.29 < *p* < 0.80). More details on the baseline values in the two groups, including the secondary outcome measures, can be found in Table 3.

**Table 3 Tab3:** Characteristics of the subjects by group. Data are expressed as the mean ± *SD*. *SER* Spherical equivalent refractive error, *AL* Axial length, *CCT* Central corneal thickness, *ACD* Anterior chamber depth, *LT* Lens thickness, t/p, independent-sample t-tests were used to compare between-group parameters; G1, Group 1; G2, Group 2

	Age (y)		Gender		SER (D)		AL (mm)		CCT (µm)		ACD (mm)		LT (mm)	
	G1 G2		G1 G2		G1 G2		G1 G2		G1 G2		G1 G2		G1 G2	
Boys			27	27										
Girls			23	23										
Minimum value	8	8			-4.50	-4.50	23.35	23.13	473.4	505.4	2.86	2.76	2.97	3.05
Maximum value	12	12			-1.25	-1.00	26.59	26.86	603.0	603.6	3.80	3.76	3.60	3.61
Mean value	9.48 ± 1.36	9.50 ± 1.50			-2.68 ± 0.83	-2.72 ± 0.90	24.79 ± 0.67	24.89 ± 0.84	545.88 ± 27.99	544.53 ± 25.78	3.28 ± 0.22	3.23 ± 0.19	3.31 ± 0.16	3.33 ± 0.14
t value	-0.07				0.22		-0.69		0.25		1.06		-0.88	
*p* value	0.94				0.83		0.49		0.80		0.29		0.38	

### Lens adaptation

All subjects adapted well to both SAL lenses and single vision lenses (Table 4). The mean DCVA at the dispensing visit was 0.06 ± 0.08 logMAR (range: -0.14 to 0.24 logMAR) in Group 1 (SAL lenses) and 0.04 ± 0.05 logMAR (range: -0.1 to 0.14 logMAR) in Group 2 (single vision lenses, SVL), with no significant difference between the groups (t = 1.11, *p* = 0.27).

**Table 4 Tab4:** Adaptation to the SAL and single vision lenses. *DCVA* Distance-corrected visual acuity. Data expressed as the mean ± SD. Group 1: in phase one for Group 1, the subjects wear the SAL lenses; Group 2: in phase one for Group 2, the subjects wear single vision lenses (SVL)

	SAL	SVL	t value	*p* value
DCVA	0.06 ± 0.08	0.04 ± 0.06	1.11	0.27
Perception of ghost images	1.04 ± 0.20	1.00 ± 0.00	1.43	0.16
Comfort of spectacles	9.68 ± 0.55	9.84 ± 0.42	-1.64	0.11
Clarity of vision	9.70 ± 0.58	9.93 ± 0.25	-2.59	0.01
Vision satisfaction	9.72 ± 0.50	9.91 ± 0.29	-2.32	0.02

For the perception of ghost images, we found no significant difference between the lens types (mean values: 1.04 ± 0.20 for SAL lenses and 1.00 ± 0.00 for SVL lenses; t = 1.43, *p* = 0.16). Similarly, there was no significant difference in the comfort of the spectacles (mean values: 9.68 ± 0.55 for SAL lenses and 9.84 ± 0.42 for SVL lenses; t = -1.64, *p* = 0.11). Regarding clarity of vision and vision satisfaction, small but significant differences were observed between the two lens types. The subjects rated single vision lenses as providing higher clarity of vision (mean values: 9.70 ± 0.58 for SAL lenses and 9.93 ± 0.25 for SVL lenses; t = -2.59, *p* = 0.01) and vision satisfaction (mean values: 9.72 ± 0.50 for SAL lenses and 9.91 ± 0.29 for SVL lenses: 0.19; t = -2.32, *p* = 0.02).

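### V1 distance acuity was collected but is neither tabulated nor used at dispensing: the balance statement has no displayed support for it, and the lens comparison gives up precision

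*Protocol article*

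**What the plan says.** All references are to the Protocol article.

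- **Collection.** Table 1 marks DCVA at every visit from V1 to V7. Study visits and procedures says that V1 acquired "all secondary outcome measures (DCVA, AL, CT, ACD, and LT").
- **Condition of measurement.** Secondary outcome measures says DCVA is read "with usual correction or new distance prescription". It does not say which of the two applied at V1.
- **Baseline balance.** Between-group comparison of baseline data (below Figure 2) states: "There were no significant differences between the groups for any of the secondary outcome measures", with -0.88 < t < 1.06 and 0.29 < p < 0.80. It adds: "More details on the baseline values in the two groups, including the secondary outcome measures, can be found in Table 3". The columns of Table 3 are age, gender, SER, AL, CCT, ACD and LT. Table 2, to which Overall baseline data also sends the reader for secondary outcomes, has no DCVA column either.
- **Lens comparison.** Lens adaptation reports V2 readings only: "The mean DCVA at the dispensing visit was" 0.06 ± 0.08 logMAR (SAL) and 0.04 ± 0.05 (single vision; Table 4 prints ± 0.06), with t = 1.11 and p = 0.27. The method named for between-group comparisons is the independent-sample t test.
- **Use made of it.** The abstract reports p = 0.27, and the Discussion concludes that SAL lenses leave DCVA uncompromised.

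**The concern.** Children differ in acuity for reasons unrelated to the lens. A V1 reading taken before any study lens captures part of that variation and cannot have been affected by the lens. Leaving it out of the V2 comparison keeps that variation in the error term. It also leaves the reader unable to see whether one group began with better acuity.

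This matters because DCVA is the secondary outcome on which the article makes its visual-performance claim, and that claim rests on a non-significant test. The reader is sent to two tables for baseline secondary outcomes and does not find this one there.

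**Working it through.** **Inputs.** V2 SDs are 0.08 (SAL) and 0.06 (single vision, Table 4; 0.05 in the text). Groups of 50 come from Between-group comparison of baseline data; I assume all 50 per group contributed a V2 reading. One letter is 0.02 logMAR (Secondary outcome measures). The V1-V2 correlation r and the V1 SD are not in the documents and are assumptions below.

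**1. Reproducing the stated test.** SE = sqrt((0.08² + 0.06²)/50) = 0.0141, or 0.0133 with SD 0.05. The printed means differ by 0.02, which gives t = 0.02/0.0141 = 1.41 (p = 0.16), or 1.50 (p = 0.14) with SD 0.05. Because means and SDs are rounded to two decimals, t can lie anywhere from 0.66 to 2.43. The stated 1.11 is inside that range, and t = 1.11 on 98 df gives p = 0.27. The stated result therefore agrees within rounding.

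**2. Difference and interval.** 1.11 × 0.0141 = 0.0157 logMAR (0.0148 with SD 0.05). The half-width is 1.98 × 0.0141 = 0.028, or 1.4 letters. The 95% CI is about -0.012 to 0.044, so the upper limit is about 2.2 letters.

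**3. Precision from adjustment.** ANCOVA SE = 0.0141 × sqrt(1 - r²). The t column is 1.11/sqrt(1 - r²), which applies if the groups had equal V1 means.

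| Assumed r | SE | Reduction | 95% half-width | t (p), no V1 imbalance |
|---|---|---|---|---|
| 0 | 0.0141 | none | 0.028 | 1.11 (0.27) |
| 0.3 | 0.0135 | 5% | 0.027 | 1.16 (0.25) |
| 0.5 | 0.0122 | 13% | 0.024 | 1.28 (0.20) |
| 0.7 | 0.0101 | 29% | 0.020 | 1.55 (0.12) |

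**4. How much a V1 imbalance would carry over.** With similar SDs at V1 and V2 the regression slope is about r. An imbalance of one SE (0.0141) then shifts the V2 difference by r × 0.0141:
- r = 0.3: 0.004, or 27% of 0.0157
- r = 0.5: 0.007, or 45%
- r = 0.7: 0.010, or 63%

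At r = 0.7 the adjusted difference would be 0.0157 - 0.0099 = 0.0058 (t = 0.0058/0.0101, about 0.6) or 0.0157 + 0.0099 = 0.0256 (t about 2.5), depending on which group started better.

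**5. What the balance sentence shows.** Its bounds are the Table 3 entries for LT (t = -0.88), ACD (t = 1.06, p = 0.29) and CCT (p = 0.80). If V1 DCVA was tested and fell inside them, and its SD was 0.05 to 0.08 (assumed), the V1 difference is at most 1.06 × SD × sqrt(2/50) = 0.011 to 0.017. The resulting shift is 0.003 to 0.012 for r from 0.3 to 0.7.

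**The case against.** The strongest reply is that allocation was randomized 1:1, so the unadjusted t test is valid and its standard error already allows for chance imbalance. That stands. A reader might infer that the comparison cannot tell a lens effect from a baseline difference, or that any V1 imbalance passes in full into the V2 result. Neither follows: the test is unbiased over randomization, and only the correlated part of an imbalance carries over (step 4).

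A reader might also infer that DCVA was left out of the balance check, since the quoted bounds match three other variables. The documents do not show this. Bounds identify only the extremes. AL, also listed among the secondary measures at V1, has t = -0.69 and p = 0.49, inside the bounds and invisible in them. DCVA could sit there too. What is established is that it is not displayed.

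The size of the gain is also open to challenge. "The inclusion criteria were best-corrected visual acuity equal to or better than 1.0": this restriction may narrow the spread of V1 acuity and lower r, and at r = 0.3 the gain is small. The V1 reading may have been taken with the usual correction, which would weaken it further; 27 children reported no earlier detection or correction of their myopia (Family history and supplementary information). This limits the benefit but does not remove it, because a covariate measured before any study lens is legitimate whichever correction was worn, provided the condition is stated.

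Finally, with no V1 imbalance the test stays non-significant across the range of r examined, and this is an adaptation check rather than the efficacy analysis. Both points are fair and keep the concern modest. The first depends on there being no imbalance, which is what the article does not show.

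**Conclusion.** The point holds as a reporting gap together with an avoidable loss of precision. It is not a flaw in validity. V1 DCVA is described as acquired, is missing from both tables said to contain the baseline secondary outcomes, and is unused in the comparison behind the acuity conclusion. That conclusion rests on a difference of about 0.016 logMAR with a 95% CI of about -0.012 to 0.044.

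Adjustment would narrow the interval by about 5% to 29% for r from 0.3 to 0.7. It could also move the estimate by an amount that depends on a V1 difference the reader cannot see. These sizes rest on the assumed r, on similar SDs at V1 and V2, on 50 readings per group, and on the Table 4 SD; using 0.05 from the text changes the SE only to 0.0133.

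**What to change.** 1. Add V1 DCVA by group to Table 3 and state which correction was worn. If that cannot be done, limit the balance sentence to the variables the table shows.
2. Report the V2 DCVA difference from an ANCOVA with lens group as factor and V1 DCVA as covariate, giving the adjusted difference and its 95% CI. Prefer the V1 reading with the new distance prescription where it exists; otherwise use the reading that was taken and say so. A plain change score is a poorer choice, since with similar SDs it beats the raw comparison only if r exceeds 0.5.
3. Word the Discussion's acuity conclusion in terms of that interval.

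The cost is one table row and one re-run, using V1 readings the article describes as already taken. The p value in the abstract may move in either direction.
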